### *5.5 Key inclusion criteria*

Patients must meet the following criteria to be eligible for the study:

1) Be admitted to HUP or PPMC; 2) Born between 1945 and 1965

### *5.6 Key exclusion criteria*

Patients will be excluded if they have already received HCV screening or have been previously diagnosed with HCV.

## **6. Subject recruitment**

This is a pragmatic study of a health system intervention. Clinicians and patients will be exposed to the intervention as a part of their usual care during inpatient hospital admission.

## **7. Subject compensation**

No compensation will be offered in this study.

## **8. Study procedures**

### *8.1 Consent*

A waiver of informed consent is requested. This is a health system initiative that will be implemented. The study is to evaluate that initiative. Therefore, physicians and their patients will not be consented as this is the standard of practice per the health system initiative. Without a waiver of the consent, the initiative would still be implemented by the health system, but the study would be infeasible. There are several additional reasons why we feel a waiver of consent should be granted. First, it is not feasible to consent every patient and physician and as mentioned this initiative would occur with or without the study of it. Second, if members of the control group were consented, they would know they were being studied and this could change their behavior. This could potentially disrupt the design of the study and making interpretation of the findings challenging. Third, physicians are not being forced to order HCV screening for their patients. Instead, they are being reminded of evidence-based CDC and USPSTF guidelines and Pennsylvania Law and offered an opportunity to order HCV screening. This is no different than standard of care in which a physician would review the same information and decide to pursue HCV screening or not.

### *8.2 Procedures*

Data on clinicians and their patients at the University of Pennsylvania Health System will be obtained from Penn Data Store and Clarity (Epic's data reporting database). Physician data

includes demographic information (age, race, gender, type of medical degree, etc.) and may be also obtained from publicly available databases or websites online. Patient information includes demographic information, information about comorbid conditions (including diabetes, hypertension, and chronic liver disease, and comorbid conditions needed to calculate the Charleston Comorbidity Index and laboratory test results (HCV antibody and viral load) and medications to treat HCV.

## **9. Analysis plan**

All analyses will be conducted using intention-to-treat using the patient as the unit of analysis. All hypothesis tests will use a two-sided alpha of 0.05 as our threshold for statistical significance.

The primary outcome measure will use a binary indicator representing the presences of HCV screening or not for each patient. In the main adjusted analysis, we will fit models using generalized estimating equations using group (HUP or PPMC), period (3-month increment) fixed effects, and a variable for intervention (default implemented or not) and adjusting for temporal trends.

To test the robustness of our findings, we will perform sensitivity analyses that adjusts for available patient characteristics and comorbidities such as demographics and the Charlson Comorbidity Index.

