## **5. Study design**

### *5.1 Design*

This study will use a stepped-wedge cluster randomized clinical trial to evaluate a health system initiative to improve inpatient HCV screening. We will randomly assign either the Hospital of the University of Pennsylvania (HUP) or Penn Presbyterian Medical Center (PPMC) to have the default intervention implemented in the admission order set within the electronic health record (EHR). Clinicians will have the opportunity to opt out and not order the screening test. There will be 3 wedges, each 3 months in duration, including a 3-month pre-intervention period, a 3-month period where only the site randomly selected to go first will have the intervention implemented, and then a 3-month period where both sites will have the intervention implemented. We will also look retrospectively at HCV screening rates before and after the EHR alert was implemented on May 14, 2019.

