### *5.4 Accrual*

Based on data from early 2020, we expect about 1500 patients per site over a three month period. Therefore, we estimate that for HCV screening, we will have 90% power to detect a 9.6-percentage point difference and 80% power to detect an 8.2 percentage point difference. This assumes a baseline rate of 20% and a 2-sided  $\alpha$  of 0.05 as our threshold for statistical significance. For detecting viral load positive patients, we estimate that we will have 90% power to detect a 3.7-percentage point increase and 80% power to detect a 2.9-percentage point

increase. This assumes a baseline rate of 0.5% and a 2-sided  $\alpha$  of 0.05 as our threshold for statistical significance.

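### The single on/off intervention term recovers the default's effect only if that effect is the same in exposure months 1-3 and 4-6; otherwise the estimate falls outside both

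*Protocol*

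**What the plan says.** Section 5.1 randomises the order in which two hospitals receive the default. The timetable is fixed: "There will be 3 wedges, each 3 months in duration, including a 3-month pre-intervention period". The second wedge is described as "a 3-month period where only the site randomly selected to go first will have the intervention implemented". For the third wedge the text reads "then a 3-month period where both sites will have the intervention implemented". So in wedge 3 the first hospital is in its second quarter of exposure while the second hospital is in its first.

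Section 9 specifies the main adjusted analysis as "generalized estimating equations using group (HUP or PPMC), period (3-month increment) fixed effects". The treatment term that goes with these is described as "a variable for intervention (default implemented or not) and adjusting for temporal trends". The link function is not named. There is no term for time since implementation. The only sensitivity analyses listed add patient characteristics and comorbidities. The assumption that the effect is constant over exposure time is not stated.

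**The concern.** A 0/1 term treats the first hospital in months 4-6 and the second hospital in months 1-3 as receiving the same effect. If the effect differs between those two stages, wedge 3 is no longer a neutral comparison. The first hospital's later result enters the estimate with a negative sign, so the better the default does in months 4-6, the smaller the reported effect.

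At stake is the trial's main number. A default that gains force would look weaker than it was in any quarter, and one that loses force would look stronger than it was in any quarter. Nothing else in the stated analysis would show this.

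**Working it through.** The protocol states no figure for how the model weights the data, so there is none to reproduce. The weights follow from the design.

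**Inputs.** Two hospitals, one per sequence, and three wedges (5.1). Hospital effects, period effects and one 0/1 term (9). "we expect about 1500 patients per site over a three month period" (5.4), which gives six equal cells. Baseline screening 20% (5.4). Outcome: change in percentage screened (3.1), so the risk-difference scale is used first.

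**Step 1: what the coefficient estimates.** Least squares on the six cells gives these weights:

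| | Wedge 1 | Wedge 2 | Wedge 3 |
|---|---|---|---|
| First hospital | −0.5 | +1 | −0.5 |
| Second hospital | +0.5 | −1 | +0.5 |

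Let G1, G2, G3 be the first-minus-second hospital gaps in the three wedges. The coefficient is G2 − (G1 + G3)/2.

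**Step 2: let the effect vary with exposure time.** Let g be the gap between the hospitals without the default. Then G1 = g, G2 = g + d1 and G3 = g + d2 − d1.

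Coefficient = d1 − 0.5·(d2 − d1) = 1.5·d1 − 0.5·d2 = d1 + 0.5·(d1 − d2).

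| d1 (points) | d2 (points) | Coefficient |
|---|---|---|
| 10 | 10 | 15 − 5 = 10 |
| 20 | 22 | 30 − 11 = 19 |
| 10 | 20 | 15 − 10 = 5 |
| 20 | 10 | 30 − 5 = 25 |

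Patient-level GEE with an identity link gave 5.0 points for 10 then 20, under independence and exchangeable working correlation alike.

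**Step 3: do trend terms help?** A trend common to both hospitals is absorbed by the period effects. A hospital-specific linear trend leaves the weights unchanged, because −0.5, +1, −0.5 already sums to zero against a straight line.

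**Step 4: how exact are 1.5 and −0.5?** Hospitals of different but stable size (2000 against 1000 per wedge) give the same weights. In two scenarios with volume varying by wedge, the weights were 1.47/−0.47 and 1.55/−0.55. Under a logit link, with 20% rising to 30% then 40%, the coefficient is 0.280. The formula gives 0.318, and the true log-odds effects are 0.539 and 0.981. The coefficient is still below both.

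**Step 5: separate terms for the two exposure quarters.** These are estimable, but they use up all six cells.

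- Months 1-3: G2 − G1, the wedge 1-to-2 difference-in-differences.
- Months 4-6: (G2 − G1) + (G3 − G1).

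Variance factors, as sums of squared weights in units of p(1 − p)/n:

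- Planned coefficient: 4 × 0.25 + 2 × 1 = 3.
- Months 1-3: 4 × 1 = 4, so the SE ratio is √(4/3) = 1.15.
- Months 4-6: 2 × 4 + 4 × 1 = 12, so the SE ratio is √(12/3) = 2.

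With 1500 per cell and no allowance for clustering, the detectable difference at 80% and 90% power is 5.2 and 6.1 points for the planned coefficient, and 5.9 and 6.9 for the months 1-3 term.

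**Step 6: the competing explanation.** Suppose instead that the effect is constant in time but is A at the first hospital and B at the second. Then G2 − G1 = A and G3 − G1 = A − B.

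- Planned coefficient: A − 0.5·(A − B) = (A + B)/2.
- Months 1-3 term: A.
- Months 4-6 term: 2A − B.

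With A = 10 and B = 20 these are 15, 10 and 0. A changing effect and a between-hospital difference both act through G3 − G1 alone, so six cells cannot tell them apart.

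**The case against.** The planned model is a conventional stepped-wedge model, it contradicts nothing else in the protocol, and it is unbiased if the effect is constant. The protocol gives no evidence that the effect will change. Section 4 presents defaults as fitting workflow without requiring action, which if anything suggests stability. A modest drift does modest harm, as 20 then 22 giving 19 shows. A statistical analysis plan, not available here, may add an exposure-time analysis. All of this stands, and it limits the point to an unstated assumption in a main model that the protocol does fix.

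A reader might go further and infer that the wedge 1-to-2 difference-in-differences should become the primary estimate. The documents do not support that. It would discard wedge 3 and say nothing about the second hospital's response. If the hospitals respond differently but stably, the planned coefficient is their plain average, whereas the two-term model would show a false fade (step 6).

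Two other readings also fail. The protocol does not say that it will report an average effect over exposure time. Nor can the 5.9 and 6.9 points be called safely within the 8.2 and 9.6 points stated in 5.4. The stated figures do not reproduce at patient level and may carry an unstated clustering allowance, so the two sets are not comparable.

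**Conclusion.** The point holds as a conditional weakness in a specified main analysis. The coefficient departs from the months 1-3 effect by half of d1 − d2, and from the simple mean of the two effects by the whole of it: 1.5·d1 − 0.5·d2 − (d1 + d2)/2 = d1 − d2. The direction is known: too low for growth, too high for fade.

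This rests on the risk-difference scale, stable volumes at each hospital, and the same d1 at both hospitals. A logit link or varying volumes changed the size in the cases examined. Under the logit link the direction and the out-of-range position were unchanged. Whether d1 and d2 will differ is unknown. The finding is that the plan relies on their equality without saying so and names no analysis that would reveal a departure.

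**What to change.** In section 9, keep the single-indicator model as the main analysis and add three things.

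1. State that its coefficient assumes the same effect in exposure months 1-3 and months 4-6.
2. Prespecify as a sensitivity analysis a model with separate indicators for months 1-3 and months 4-6. Report both terms beside the main coefficient, noting that the months 1-3 term is the wedge 1-to-2 difference-in-differences.
3. State that if the main coefficient and the months 1-3 estimate differ materially, the main coefficient will not be read as the default's effect without qualification, and that the difference may reflect either change over exposure time or a difference between hospitals.

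No change to design, data or sample size is needed. The costs are in interpretation. The months 1-3 estimate is somewhat less precise (SE about 15% larger at equal variances) and reflects only the first hospital's first quarter. The months 4-6 estimate has twice the SE of the planned coefficient and suits supporting use only. With one hospital per sequence, the sensitivity analysis can flag a problem but cannot identify its cause.

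### The main model leaves out patient characteristics that are already being collected, although two hospitals and three wedges give it no other protection against a change in case mix at one hospital

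*Protocol*

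**What the plan says.** Section 9 of the Protocol (Analysis plan) analyses screened or not screened, "using the patient as the unit of analysis". For the main adjusted analysis it states: "we will fit models using generalized estimating equations using group (HUP or PPMC), period (3-month increment) fixed effects, and a variable for intervention", then "and adjusting for temporal trends". No patient-level covariate is listed. The next paragraph places such covariates in a robustness check: "we will perform sensitivity analyses that adjusts for available patient characteristics and comorbidities such as demographics and the Charlson Comorbidity Index".

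Section 5.1 (Design) names two hospitals and draws at random which one goes first. On timing it says: "There will be 3 wedges, each 3 months in duration". Section 5.4 (Accrual) gives the size of each hospital-by-period cell: "we expect about 1500 patients per site over a three month period". Section 8.2 (Procedures) confirms that demographics and comorbidities will be extracted for each patient, so the data for an adjusted main model will be there.

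**The concern.** Hospital effects remove stable differences between the two sites, and period effects remove changes that both share. Neither touches a change in patient mix at one hospital in one wedge. In a trial with many clusters such changes tend to average out. Here there are two hospitals and one random ordering, so nothing averages.

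Adjustment for measured patient characteristics is the protection left. The plan has the data but uses them only in a secondary analysis. If the two analyses differ, the trial would draw its conclusion from the less protected one.

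**Working it through.** **The plan's own figures.** Section 5.4 gives detectable differences of 9.6 points (90% power) and 8.2 points (80% power) from a 20% baseline, two-sided 0.05. These were not reproduced. With 1500 per group a two-proportion comparison has over 99.9% power at both. The two-hospital, three-period model with 1500 per cell has about 99.9% and 99%. The stated figures are therefore conservative and may contain an unstated allowance for clustering. They do not affect this point, except that they imply a larger standard error: 8.2 / (1.960 + 0.842) = about 2.9 points.

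**What the main model estimates.** Let A be the hospital that goes first, B the other, and A1 to B3 the six cell screening rates (equal cells, percentage-point scale). Take the between-hospital difference in each wedge, with s the stable site difference and θ the intervention effect:

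- wedge 1 (neither exposed): A1 − B1 = s
- wedge 2 (only A exposed): A2 − B2 = s + θ
- wedge 3 (both exposed): A3 − B3 = s

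Least squares gives θ̂ = (A2 − B2) − ½[(A1 − B1) + (A3 − B3)].

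**How a case-mix change at hospital A passes through.** Suppose it moves A's screening rate by d:

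| Pattern | Effect on θ̂ |
|---|---|
| Wedge 2 only | +d |
| Wedge 1 only or wedge 3 only | −½d |
| Lasting step from wedge 2 on | d − ½d = +½d |
| Linear drift 0, d, 2d | d − ½(2d) = 0 |

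Signs reverse for hospital B.

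**Whether the temporal-trend term helps.** The model with hospital, period and intervention has rank 5 for six cells. A common linear trend is already contained in the period effects, so the rank stays 5. A hospital-specific linear trend raises the rank to 6 but leaves the intervention weights unchanged. Either way, the change passes through as in the table. The Protocol does not state a link function. On the logit scale the same pattern holds: under no effect, a 2-point rise in A2 moves the log odds ratio by 0.12, and a 2-point rise in A1 or A3 moves it by −0.06.

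**Size (assumed; the documents give no case mix by hospital or period).** Shift = change in a subgroup's share × difference in its screening rate.

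- Low: 0.05 × 0.10 = 0.5 points in wedge 2, so 0.25 points in wedge 1 or 3.
- High: 0.10 × 0.20 = 2.0 points in wedge 2, so 1.0 point in wedge 1 or 3.

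**Reference standard error.** The squared weights sum to 1 + 1 + 4 × 0.25 = 3. With p = 0.20 and independent patients, SE = √(3 × 0.20 × 0.80 / 1500) = 1.79 points.

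**Effect on the test.** Given a 2-point shift in wedge 2 and no intervention effect, the nominal 5% two-sided test rejects about 20% of the time at SE 1.79 (2 / 1.79 = 1.12). At SE 2.9 it rejects about 10% of the time. A 1-point shift gives about 8.6% and 6%.

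**Precision.** Covariates explaining 5 to 10% of the outcome variance cut the SE by 1 − √(1 − R²), about 2.5 to 5%. That is a modest gain and not the main reason to change.

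**The case against.** **It is a choice of label.** The adjusted analysis is prespecified, both results will be produced, and a measured shift would show up when they are compared. This stands as far as it goes: the plan contains no contradiction and no arithmetic error. But the label decides which estimate the trial concludes from. The exact covariate list and look-back window may properly sit in an analysis plan that is not shown, so their absence is not criticised here.

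**It is not bias.** A reader might infer that the main estimate is systematically biased. The documents do not support that. The hospital that goes first is drawn at random, so a shift unrelated to the draw is equally likely to push the estimate up or down and averages zero over the randomisation. It is extra error. Zero mean does not make it harmless to the test, since a two-sided rejection rate rises equally for either sign. One allocation-related route can be imagined: sections 5.3 and 5.6 exclude patients already screened, so a working default could thin out returning patients at the first hospital by wedge 3. That would enter at half weight. The Protocol gives no readmission figure from which to size it, and covariates would address it only in part.

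**Full pass-through is the worst case.** This is correct. Full size applies to wedge 2 alone. It is also true that main effects never remove an interaction at any number of sites; having two sites takes away only the averaging.

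**Liver disease.** Section 8.2 lists "information about comorbid conditions (including diabetes, hypertension, and chronic liver disease" among the extracted data. A reader might infer that the plan will adjust the antibody and viral-load outcomes for a condition that screening itself can reveal. Section 9 does not say so: its named examples are demographics and the Charlson index, and its modelling text describes only the primary outcome.

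**The covariates may be weak.** Age is already restricted by the 1945 to 1965 birth cohort, and unmeasured changes stay. Both are fair limits on the benefit.

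**Conclusion.** The point holds as a weak choice of primary analysis for this design. Neither the hospital and period effects nor the temporal-trend term removes a case-mix change at one hospital, and with two hospitals it cannot average out. Under the assumed inputs the error is 0.5 to 2.0 points for a wedge-2 change and 0.25 to 1.0 point for one in wedge 1 or 3. This is well below the 8.2 to 9.6 points the trial is planned to detect, but at the upper end it is comparable with the patient-level standard error of 1.79 points. The pass-through fractions assume equal cells and a percentage-point scale. The documents show no actual shift and give no basis for choosing within the range. The finding is avoidable chance error in the headline estimate, not demonstrated bias.

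**What to change.** In section 9, make the primary analysis the hospital, period and intervention model that also adjusts for a short prespecified set of patient covariates: age, sex, race and the Charlson index. Take the comorbidities only from records dated before the index admission, so that nothing adjusted for can follow from the screening test. Report the result as a standardised percentage-point difference, and keep the hospital and period model without patient covariates as the sensitivity analysis. State that adjustment addresses measured case mix only. If a separate analysis plan already does this, bring the Protocol into line with it.

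The cost is analysis wording, settled before outcome data are examined, plus a missing-category rule for incomplete demographics. No new data collection is needed beyond what section 8.2 already plans.

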## **11. Human research protection**

### *11.1 Data confidentiality*

Computer-based files will only be made available to personnel involved in the study through the use of access privileges and passwords. Wherever feasible, identifiers will be removed from study-related information. Precautions are already in place to ensure the data are secure by using passwords and HIPAA-compliant encryption.

### *11.2 Subject confidentiality*

Data on physicians and patients will be obtained from Epic and Penn Data Store. Any information that is obtained will be used for research purposes only. Information on patients will only be disclosed within the study team. All study staff will be reminded of the confidential nature of the data collected and contained in these databases.

Data will be stored, managed, and analyzed on a secure, encrypted server behind the University of Pennsylvania Health System (UPHS) firewall. This server was created for projects conducted by the Penn Medicine Nudge Unit related to physician and patient behavior at UPHS. All study personnel that will use this data are listed on the IRB application and have completed training in HIPAA standards and the CITI human subjects research. Data access will be password protected. Whenever possible, data will be deidentified for analysis.

### *11.3 Subject privacy*

All efforts will be made by study staff to ensure subject privacy. Data will be evaluated in a de-identified manner whenever possible.

### *11.4 Data disclosure*

Information on physicians and patients will not be disclosed to anyone outside of the study team.

### *11.5 Data safety and monitoring*

The investigators will provide oversight for the study evaluation of this health system initiative. Clinicians will follow their standards of care to manage patients admitted to the hospital.

### *11.6 Risk/benefit*

#### *11.6.1 Potential study risks*

The potential risks associated with this study are minimal. Breach of data is a potential risk that will be mitigated by using HIPAA compliant and secure data platforms for the intervention (Penn Medicine servers) and evaluation (Nudge Unit server). HCV screening is conducted as standard of care and involves a blood draw.

